### SAIA-SSP-HIV specialist activities

We will hire and train two SAIA specialists who are knowledgeable about SSPs’ organizational cultures and service delivery models. SAIA specialist training sessions will focus on building familiarity with the specific steps of SAIA, electronic data collection instruments, and the HIV-CAT. Interactive training activities will include the provision of mock data to SAIA specialists for practicing SAIA steps. SAIA specialists will receive weekly supervision from a SAIA supervisor for the duration of the 12-month implementation period.

For SSPs randomized to SAIA-SSP-HIV, SAIA specialists will partner with leadership and frontline staff to deliver the strategy over the 12-month implementation period. SAIA specialists will meet with active implementation arm SSPs twice per month for the first three months, and once per month for the remaining nine months; these meetings will take place primarily over Zoom, with one in-person meeting each quarter. Specialists will be allotted 45 hours to deliver SAIA to each SSP (3 hours per meeting: 2 for preparation, 1 for the meeting). We chose this time allotment based on the original SAIA trial and Patel et al.’s successful naloxone pilot study [28].

During initial visits to SSPs, the assigned SAIA specialist will discuss the HIV services delivery cascade and the SAIA implementation strategy in detail with SSP leadership, observe SSPs’ processes for delivering HIV services, and review data collection procedures with attention towards identifying areas to improve documentation and streamline data collection. During subsequent visits, SAIA specialists will guide SSPs in the active implementation arm through multiple iterative cycles of cascade analysis, process mapping, and CQI, as described above. With technical support from SAIA specialists, SSPs will utilize data collection instruments developed by the study team (in collaboration with SSPs involved in our pilot study [28]) to populate the HIV-CAT.

### Data collection activities

#### Implementation determinants and context variables.

Previous implementation studies, including those utilizing SAIA, have demonstrated the importance of external context, implementation climate, and leadership engagement as determinants that influence and are influenced by quality improvement approaches [28,41]. During the initial baseline survey conducted prior to randomization, we will assess all enrolled SSPs’ basic organizational characteristics (e.g., funding sources, staff size, budget), implementation climate, and leadership engagement, which are implementation determinants we have observed in our preliminary research with SSPs [28,42]. We will measure implementation climate and leadership engagement again at 12-month follow-up for all enrolled SSPs, and once more for the SAIA-SSP-HIV arm only at 18 months, marking the end of the sustainment period.

#### Fidelity variables.

Because SAIA is delivered by a SAIA specialist, SAIA fidelity assessment will occur at the specialist level (n = 2). We will utilize a mixed-methods approach harnessing simple descriptive statistics (i.e., means, medians, standard deviations, interquartile ranges) and qualitative interviews with SAIA specialists and the staff they worked with to evaluate specialists’ fidelity to the implementation strategy. As small sample sizes represent challenges for implementation strategy fidelity assessment in general, our mixed-methods approach will utilize multiple data sources and analytic techniques to triangulate fidelity findings. Specific fidelity domains will include content, coverage, frequency, duration, quality, and participant responsiveness to SAIA, which we will capture using an encounter log in which SAIA specialists will document key information regarding session frequency and duration, SAIA steps conducted in each session, SSP staff in attendance at each session, and level of SSP staff engagement during each session [28]. This encounter log will be reviewed during weekly meetings between SAIA specialists and an experienced SAIA supervisor. Additionally, on a monthly basis, SAIA specialists will complete periodic reflections, a guided discussion tool designed to document aspects of implementation including setting, contextual and environmental factors, and adaptations to the implementation plan [43]. An additional goal of our qualitative interviews, to be conducted at the end of the trial, will be to explore any potential unintended consequences of the implementation strategy (e.g., SAIA could shift SSPs’ focus toward improving HIV services at the expense of other life-saving services).

#### Primary outcome variables.

For Objectives 1 and 2, which determine the effectiveness and sustained effectiveness of SAIA-SSP-HIV compared to IAU, our primary outcomes will include the number of HIV tests conducted and the number of referrals to appropriate clinical services for HIV prevention and treatment. As such, our primary outcomes are considered core elements of implementation effectiveness, which is a multi-faceted construct encompassing the consistency, quality, and appropriateness of an innovation’s application within an organizational setting [44]. We operationalize implementation effectiveness based on Proctor et al.’s (2011) taxonomy of implementation outcomes, with reach, measured as the number of HIV tests conducted and the number of referrals, serving as a proxy for appropriateness and consistency [45]. To operationalize these outcomes, each month SSPs will receive automated electronic forms (via REDCap) to submit data on the numbers of participant encounters, HIV tests conducted, and referrals to appropriate clinical services. SSPs will receive financial incentives every three months for timely and complete monthly data submissions [28].

#### Cost and cost-effectiveness variables.

To assess cost and cost-effectiveness of SAIA-SSP-HIV, we will utilize a modified version of the substance abuse services cost analysis program (SASCAP) [46], a validated instrument that has been applied to numerous behavioral and public health interventions involving cost and labor components [47–49]. The cost component includes questions about program costs (e.g., building and material costs), and the labor component assesses labor allocation (e.g., staff roles and salaries) across services. In addition, we will collect information on the time spent training staff and carrying out study-related activities (e.g., hours spent collecting and reporting data and meeting with SAIA specialists). Cost data will be collected monthly, and resource use questions will be integrated within the study’s fidelity and other process data collection tools. Additional cost data on building space and staff type wages will be collected at baseline and 12-month follow-up. Consistent with our other outcomes, the average cost of SAIA implementation will be assessed at the organization level.

### Data management

As detailed above, we will use REDCap, a secure online platform, for managing study data for this project. Throughout SSPs’ 21 months of enrollment, representatives of enrolled SSPs will receive monthly automated electronic forms (via REDCap) to submit outcome data on the numbers of participant encounters, HIV tests conducted, and referrals to appropriate clinical services. SSPs will receive financial incentives every three months for timely and complete monthly data submissions. One to two weeks prior to the end of the three-month lead-in period, we will also ask representatives of enrolled SSPs to complete interviewer-administered baseline surveys (via Zoom); interviewers will enter data into REDCap. To randomize programs at the end of the lead-in period, we will use REDCap’s online randomization module to randomly assign SSPs to receive SAIA-SSP-HIV or IAU. Interviewer-administered follow-up surveys will also use REDCap for data entry and management.

### Analyses and power calculations

Statistical analyses will be conducted in Stata (College Station, TX) using a single-blinded approach. Before model fitting under Objectives 1 and 2, we will assess whether there is significant variation across the three (potential) levels of aggregation for each set of key outcomes and implementation measures: (1) within-SSP level (repeated measures over time), (2) between-SSP level, and (3) SSP type (local health jurisdiction/clinic or community-based organization). We will also assess changes in outcomes over time by examining functional form. We assume that there will be piecewise linear change during the three-month lead-in period, post-implementation from baseline through 18 months, and treatment effect “deterioration” between 12 and 18 months, though non-linear functional forms may be necessary given the large number of assessments. We will also account for the total number of participant encounters for the number of HIV tests conducted outcome, and the number of HIV tests conducted for the number of referrals outcome.

For Level 1 (within-SSP), we will estimate three random effects as growth over time. On the basis of the structure of the time steps with *α*_pis_, we will estimate a random intercept (*π*_*0is*_), which is the estimated (conditional) mean value of the outcome at time =  0 (e.g., run-in baseline) and two random slopes (*π*_*1is*_*, π*_*2is*_): (1) the estimate per-year change in Y from the run-in phase through 18 months and (2) the “deterioration” phase, capturing how much reduction there is in change over the last year, if any, for the SAIA arm. These values will vary across SSP *i* within county *s*. In Level 2 (between-SSP), the Level-1 intercept and slopes will be the outcomes at Level 2.

*Β*_*pqs*_ is a matrix of coefficients corresponding to the effect of between-individual predictor *q* on Level-1 outcome *p* (intercept, slope) within SSP *s*. The key predictor included in *χ*_*qis*_ is a 0/1 dummy indicator indicating whether SSP *i* was in the SAIA condition or IAU. *Β*_*1s*_ will capture the average change over time in HIV testing and referrals to appropriate clinical services for HIV prevention and treatment, which (1) should not be significantly different from zero during the lead-in period, and (2) will vary by SAIA and IAU after implementation (by virtue of the SAIA x time period 1 interaction). *Β*_*0s*_ will capture the conditional mean level of study outcomes, which, if it varies by treatment condition, would capture a mean shift in our study outcomes. *Β*_*2s*_ will capture the change over time in study outcomes during the sustainment period; if it interacts with the SAIA indicator, it will capture slope differences over time beyond 1 year between SAIA and the IAU condition, with Year 1 gains maintained if this parameter estimate is not significant. Level 3 will capture SSP type-level variability in intercepts and, if necessary, slopes over time.

The main analyses will be modeled under full information maximum likelihood and supplemented by multiple imputation for missing data on key predictors for models under Objectives 1 and 2. Both produce accurate estimates and standard errors under the assumption that missingness is predictable by variables that are observed but unrelated to the values that are missing themselves (i.e., missing-at-random). Results from outcomes analyses across 20 multiply-imputed datasets are then combined, accounting for both between-imputation and within-imputation variation. In assessing sensitivity to the missing-at-random assumption, we may explore latent pattern mixture models for non-ignorable missingness. These methods have been utilized in other studies conducted by members of the research team.

We structured a Monte Carlo power analysis for Objectives 1 and 2 by structuring a population model reflecting weekly assessments for a 3-month lead-in period, a 12-month active intervention phase, and a 6-month sustainment period. The mean and standard deviation of the number of people who test for HIV in the target SSPs was 7.32 (2.94); these values were used as the run-in period mean and SD in the simulation. Effect sizes from a pilot study that used a similar SAIA platform ranged from.48 to 1.50; thus, we power the current study in anticipation of large effect sizes (d = .8). The mean shift in post-implementation outcomes favoring SAIA that corresponds to an effect size of.8 would be an additional 2.35 people tested under SAIA. The per-week increase in number tested under SAIA to reach a longitudinal Cohen’s d effect size of.8 by 11 weeks would be an increase of.21 persons per week. We generated 250 synthetic samples of n = 32 and analyzed the samples in Mplus while imposing (a) the random effect structure from pilot estimates and (b) a state-level ICC of.05. Power to detect a post-implementation mean shift and differences in slopes over time were greater than 80%. Detecting treatment effect deterioration from months 1–12 to month 13–18 for power of.80 requires deterioration equivalent to a Cohen’s d of.48; despite a sample size of 32, the extremely large number of repeated measures offsets the sample size with regard to statistical power to detect slope differences.

We will calculate cost estimates for each SAIA step at each SSP. For each step we will multiply the quantity of the resource (e.g., labor) used by its price (e.g., wage), then calculate the average cost for each step and all five steps for an SSP. Our effectiveness measures for the cost-effectiveness analysis (CEA) are the number of HIV tests conducted (H3.1) and the number of referrals to appropriate clinical services for HIV prevention and treatment (H3.2). Following the Second Panel of Cost Effectiveness in Health and Medicine’s recommendations, we will combine the cost estimates with the estimated change in outcomes, such as the average number of HIV tests conducted at 12 and 18 months. For CEA, we will compare cost and outcomes from the two study arms, listing each arm in order of increasing cost; we expect the IAU arm will be lower cost and listed first. To derive the cost-effectiveness ratios, we will calculate the difference in costs and outcomes between the two arms. The incremental cost-effectiveness ratio (ICER) will then be calculated as the ratio of the difference in costs to the difference in outcomes (e.g., if effectiveness is defined as the number of referrals to appropriate clinical services for HIV prevention and treatment, the ICER represents the incremental costs per additional referral). We will calculate cost-effectiveness acceptability curves (CEACs) that incorporate the inherent joint variability of the cost and effectiveness estimates and show the probability that the strategy is cost-effective as a function of the policymaker’s intrinsic valuation or willingness to pay for the outcome. Non-parametric bootstrap methods will be used to calculate CEACs.

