We designed a randomized controlled trial (RCT) to test the effectiveness of an evidence-based implementation strategy, the Systems Analysis and Improvement Approach (SAIA), in increasing SSPs’ provision of HIV testing and referrals to appropriate clinical services, which, depending on HIV test results, could involve prevention or treatment services (e.g., pre-exposure prophylaxis or antiretroviral therapy). SAIA is a flexible, multicomponent implementation strategy that supports frontline service providers by providing a comprehensive view of care delivery cascades, helping to identify areas for improvement, and iteratively testing approaches to improve quality of care [26]. In the context of HIV services, SAIA has been shown to improve the delivery of services for preventing mother-to-child HIV transmission in Mozambique, where it was also deemed acceptable among providers [27]. Recently, members of our research team adapted and pilot tested SAIA for improving the naloxone delivery cascade within SSPs, demonstrating its potential within this nonclinical community setting [28]. However, numerous differences exist between the delivery of HIV services in clinical settings SSPs, and between naloxone and HIV services delivery (e.g., staff capacity, resource and infrastructure availability, relative prioritization, complexity, standardization), warranting a need for additional implementation research on the SAIA strategy for increasing HIV services delivery within SSPs.

We developed SAIA-SSP-HIV to improve HIV services delivery among SSPs across the United States. As there is wide variation in SSPs’ provision of HIV services, and few SSPs can provide clinical services directly onsite, we focus our efforts on increasing HIV testing and the subsequent provision of referrals to appropriate clinical services depending on HIV test results. As SAIA-SSP-HIV moves beyond individual-level interventions to target organizational-level factors that impede or promote the delivery of HIV testing and subsequent referrals, it has the potential to reinvigorate and optimize these services within SSPs, effectively reaching larger numbers of PWID and better promoting individual and population health. This protocol paper describes the rationale and methods for the ongoing SAIA-SSP-HIV implementation trial, which was prospectively registered on September 6, 2023 (ClinicalTrials.gov: NCT06025435).

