## Materials and methods

### Aims, objectives, and hypotheses

The overall aim of this study is to assess the impact of SAIA-SSP-HIV on U.S. SSPs’ delivery of HIV testing and referrals to appropriate clinical services, as compared to an implementation-as-usual (IAU) condition. The specific objectives and related hypotheses of this organizational-level interrupted time series randomized controlled implementation trial include:

To test the effectiveness of SAIA-SSP-HIV on improving SSPs’ delivery of HIV testing and referrals to appropriate clinical services (i.e., for HIV prevention or treatment, depending on HIV testing results). We hypothesize that, compared to the IAU arm, SSPs randomized to the SAIA-SSP-HIV arm will demonstrate significantly higher proportions of participants receiving HIV testing and referrals over a 12-month implementation period.To test the sustained effectiveness of SAIA-SSP-HIV on improving SSPs’ delivery of HIV testing and referrals to appropriate clinical services. We hypothesize that, compared to IAU, SSPs randomized to SAIA-SSP-HIV will sustain higher proportions of participants receiving HIV testing and referrals during a 6-month sustainment period (i.e., 6 months after the active treatment phase).To estimate the costs and cost-effectiveness of SAIA-SSP-HIV on improving SSPs’ delivery of HIV testing and referrals to appropriate clinical services. We hypothesize that SAIA-SSP-HIV will be cost-effective at increasing the proportions of participants receiving HIV testing and referrals compared to SSPs randomized to IAU.

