**Specify it:**	
**Actor**	External specialist works and facilitates discussion with the organization’s implementation team with regards to the SAIA-SSP-HIV process.
**Actions**	Identify gaps: Present data evaluating the SSP’s^a^ delivery of the HIV care cascade with HIV-CAT.^b^ Facilitate discussions and support the implementation team to identify and develop consensus with regards to the areas of attrition along the HIV care cascade that they would like to address. Identify causes and opportunities: a. Facilitate discussions with the implementation team to review the SSP’s service structure and draw process maps documenting the flow of participants through the HIV care cascade to understand (i) why there are drop-offs or inequities in distribution at different points (root causes of participant attrition) and (ii) what it would take to address those issues (opportunities to streamline workflows and address key points of attrition). b. Assist team in developing consensus about programmatic modifications based on their importance and feasibility. Conduct CQI:^c^ a. Support and mentor the implementation team in operationalizing programmatic modifications. b. Present follow-up data on the delivery of the HIV care cascade for the implementation team to assess changes resulting from programmatic modifications. c. Repeat above actions after conclusion of the cycle.
**Action target**	Leverage programmatic data to facilitate CQI and foster a learning climate.
**Temporality**	After training the implementation team on the SAIA process and integrating enhanced instruments to collect program data into workflows to track HIV care cascade delivery indicators.
**Fidelity**	Content: Specialist completes actions 1–3 with SSPs. Coverage: SSP staff are present during actions 1–3. Duration: Actions 1, 2, and 3 take ~ 60min each. Frequency: Specialist visits SSPs in person during months 1, 4, 7, and 10. Specialist meets SSPs virtually during all other months in active phase. Quality: Specialist forms rapport with SSP staff, flexibly attends to their unique needs, and motivates SSP staff to engaged with actions 1–3. Participant responsiveness: SSP staff like working with the specialist and like participating in actions 1–3.
**Targeted implementation outcomes**	Implementation effectiveness relative to IAU.^d^ Reach: Number of HIV tests conducted Fidelity (to delivery of the HIV care cascade): Number of referrals to appropriate clinical services for HIV prevention and treatment

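### The primary referral analysis accounts for the number of HIV tests, which SAIA is meant to raise, so it does not estimate the effect on referrals that the protocol names

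*Protocol article*

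**What the plan says.** Under Primary outcome variables, the protocol article states that "our primary outcomes will include the number of HIV tests conducted and the number of referrals to appropriate clinical services for HIV prevention and treatment". Both are counts.

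Under Aims, objectives, and hypotheses, Objective 1 is framed per participant: the active arm is expected to show "significantly higher proportions of participants receiving HIV testing and referrals over a 12-month implementation period".

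Under Analyses and power calculations, the tests model is to account for total participant encounters, and the referrals model for "the number of HIV tests conducted for the number of referrals outcome". The same section names referrals as an effectiveness measure for the cost-effectiveness analysis, where "the ICER represents the incremental costs per additional referral".

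Two further places fix the role of testing. Table 1 lists among the targeted implementation outcomes "Reach: Number of HIV tests conducted". The Introduction says of the trial's purpose that "we focus our efforts on increasing HIV testing and the subsequent provision of referrals to appropriate clinical services depending on HIV test results".

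**The concern.** Tests lie on the path from SAIA to referrals. The strategy aims to raise them, they are reported monthly throughout the 21 months while randomisation comes at the end of the three-month lead-in, and referral follows testing. A model that holds tests fixed asks only whether SAIA changes the number of referrals made for a given number of tests. It gives no credit for referrals that exist because SAIA brought more people to testing.

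Two things are at stake. First, one of the two primary outcomes could read as no effect when SAIA has raised referrals in just the way the Introduction describes. Second, the comparison given tests is no longer protected by randomisation. Incentives for testing are among the example solutions under Process mapping, and they can change who is tested and hence how readily a test leads to a referral.

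**Working it through.** **Inputs from Analyses and power calculations.** Run-in mean 7.32 and SD 2.94 for the number tested; effect size d = 0.8; planned shift 2.35; slope 0.21 per week to reach it by 11 weeks.

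**Plan's own figures.** 0.8 × 2.94 = 2.352, and 2.352 / 11 = 0.214. Both agree with the protocol. The planned level under SAIA is 7.32 + 2.35 = 9.67, a rise of 2.35 / 7.32 = 32%.

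**Input not in the protocol.** The referral rate per test, *r*, is not given. Values of 0.3, 0.5 and 0.7 are assumed below.

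**Case 1: same *r* in both arms.**
- Ratio of referral counts: 9.67*r* / 7.32*r* = 1.32, whatever *r* is.
- Ratio given tests: *r* / *r* = 1.00.
- True gain in referrals per week: 2.35 × 0.3 = 0.71; 2.35 × 0.5 = 1.18; 2.35 × 0.7 = 1.65.

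A simulation of 32 programs over 52 weeks (100 runs per value of *r*) gave the following. It assumed a between-program SD of 2.0 and encounters averaging 60 per week, unaffected by arm.

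| Referral analysis | SAIA effect, range over the three values of *r* |
|---|---|
| No adjustment (ratio) | 1.32 to 1.34 |
| Encounters as offset (ratio) | 1.32 to 1.34 |
| Tests as offset (ratio) | 1.00 |
| Tests as linear covariate (referrals per week) | −0.006 to 0.003 |

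The encounter row matches the unadjusted row because encounters were simulated as unaffected by SAIA.

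**Case 2: added tests lead to referral at a different rate, *m*.**
- Count ratio = (7.32*r* + 2.35*m*) / 7.32*r* = 1 + 0.321 × (*m*/*r*).
- Ratio given tests = (7.32*r* + 2.35*m*) / 9.67*r* = 0.757 + 0.243 × (*m*/*r*).

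| *m*/*r* (assumed) | Count ratio | Ratio given tests |
|---|---|---|
| 0 | 1.00 | 0.76 |
| 0.6 (e.g. 0.3 against 0.5) | 1.19 | 0.90 |
| 1.0 | 1.32 | 1.00 |
| 1.2 | 1.39 | 1.05 |

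For any *m*/*r* above 0 and below 1, the two ratios fall on opposite sides of 1. Nothing in the protocol says where *m*/*r* lies.

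**The case against.** The best defence is that referrals per test is a deliberate cascade-step measure. SAIA works on drop-offs between successive steps, Table 1 lists referrals under fidelity to the cascade and not under reach, and the analysis section uses the preceding step as the reference for each outcome: encounters for tests, tests for referrals. This makes referrals per test a sensible secondary measure. It does not make it the stated target. Table 1 still defines the outcome as a number of referrals, the primary-outcome section counts referrals as reach, and Objective 1 refers to participants, not to tests.

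The wording on accounting for tests is also open. It does not say offset, denominator or covariate, nor whether the tests are concurrent or from the lead-in. A lead-in value would leave the testing pathway intact. The parallel with encounters in the same sentence makes the concurrent reading the natural one, and the three concurrent forms all remove the pathway.

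A reader might infer more than the document supports:
- *That the trial would miss SAIA's effect on testing.* It would not. Tests are a primary outcome with their own model, and the cost-effectiveness analysis takes a between-arm difference in referrals with no stated conditioning on tests. Neither, however, is the Objective 1 test for referrals.
- *That the cost-effectiveness ratio will use the tests-adjusted coefficient.* The protocol does not say so. The point is that the two results would answer different questions.
- *That SAIA will appear harmful.* A ratio below 1 needs the added tests to lead to referral less often than existing ones. That is possible, but it rests on assumed rates.
- *That dividing by encounters guarantees the total effect.* Encounters are also reported after randomisation, and solutions that reorganise participant flow could change them.

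**Conclusion.** The point holds and should be corrected before the analysis. As stated, the primary referral model estimates an effect given a post-randomisation variable that SAIA targets, and this matches none of the three referral quantities the protocol names. At the planned 32% rise in tests, with equal referral rates per test, a 32% rise in referrals would appear as a ratio of 1.00. Those two figures rest on the equal-rate assumption and on the concurrent reading. On that reading, the loss of the testing pathway does not depend on the value of the rate. The problem concerns one of the two primary outcomes; the tests outcome is unaffected. Because the article states this rule, it is not a detail left to an analysis plan.

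**What to change.** State one primary referral analysis that does not condition on tests after randomisation, and align the hypothesis, the outcome definition and the model with it. There are two suitable choices:
- referrals per participant encounter, which parallels the tests model and is the nearest the collected data come to the per-participant hypothesis; or
- referral counts adjusted only for lead-in values, which avoids conditioning on anything measured after randomisation.

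Report whichever is not chosen as a sensitivity analysis, since SAIA could also affect encounters. Keep referrals per test as a secondary cascade-step measure, labelled as conditional on a post-randomisation variable, and say whether tests enter as an offset, a denominator or a covariate.

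The cost is a few sentences and one extra model. Encounters, tests and referrals are already collected in the lead-in and throughout follow-up, so no new data are needed.
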